#### Self-efficacy

Self-efficacy is important for individuals to adopt and maintain a program of regular physical activity. It is assessed using the self-efficacy instrument developed by Marcus et al [39]. The patient rates his/her confidence of being physically active in different types of situations on a 5-item scale with responses ranging from "not at all confident" to "extremely confident". The total score is computed by calculating the average of all 5 questions. A higher score indicates greater self-efficacy.

#### Social support

This is assessed using the social support for physical activity scale adapted from Cohen and colleagues [40]. Thirteen questions rated from 0 to 5 were used to assess the influences of family and friends on patients in the last 3 months as they performed regular physical activity. Higher scores reflect more perceived social support from these individuals.

#### Physical Activity Enjoyment

The Physical Activity Enjoyment Scale adapted from Kendzierski and DeCarlo [41] is used to evaluate enjoyment of physical activity. It is a self-administered 18-item, Likert scale used by patients to rate their current feelings about physical activity. The total scale score, computed after recoding, is obtained by summing the scores of all the items. High scores correspond to increased enjoyment, while low scores correspond to little enjoyment.

#### Adherence

Participants' attendance is monitored during each session for 12 weeks for both interventions via signing of attendance sheets. Patients are also asked to maintain daily Tai Chi or stretching exercise activity logs during the 12 week intervention and are encouraged with phone calls from the research staff to continue throughout the follow up period. At the 24 and 48 week visit, the research staff will ask about the average number of times per week and the number of minutes per session the subject practices at home.

#### Safety

Study patients are monitored weekly for the occurrence of adverse events defined as any undesirable experience during the duration of the study. Lack of effect of Tai Chi or stretching/education is not considered an adverse event. Patients are monitored weekly to determine whether an adverse event has occurred. All adverse events are recorded on an adverse event case report form.

### Statistical Analysis

The primary outcome is the measurement of change in knee pain between baseline and 12 weeks. Secondary outcomes are measurements of change at 24 weeks and 48 weeks. These will be analyzed both as individual time points and in longitudinal analyses. Analyses will be intention-to-treat with secondary analyses based on completers.

We will also explore a knee-based approach to the study that will use linear mixed models to adjust for correlations in outcome between knees. The most disabled knee will be used as the unit of analysis. One knee will be chosen at random if two knees are equally affected. Considering both knees would require accounting for the correlation between knees and for the presence of disability in only one knee for many participants. However, we will characterize individuals on the basis of unilateral vs. bilateral KOA and explore any possible influences of this characterization in secondary analyses.

For the patients who withdraw during the study, every effort will be made to complete a follow-up WOMAC and clinical knee examination at the time of withdrawal. If a withdrawal assessment cannot be made, we will carry forward the last assessment of knee pain, physical function or as a conservative assessment to bias towards the null hypothesis.

We will also perform a cost-effectiveness analysis to evaluate whether Tai Chi is a cost-effective therapy for patients with KOA. The costs will be estimated from health care utilization reported by subjects at the end of the trial using the Health Assessment Questionnaire that includes medication usage, hospitalization and health care professionals' visits. The differences in direct and indirect health care cost between the Tai Chi and attention control (wellness education and stretching) groups will also be compared.

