**Methods/Design:**

Forty eligible patients, age > 55 yr, BMI ≤ 40 kg/m^2 ^with tibiofemoral osteoarthritis (American College of Rheumatology criteria) are identified and randomly allocated to either Tai Chi (10 modified forms from classical Yang style Tai Chi) or attention control (wellness education and stretching). The 60-minute intervention sessions take place twice weekly for 12 weeks. The study is conducted at an urban tertiary medical center in Boston, Massachusetts. The primary outcome measure is the Western Ontario and McMaster Universities (WOMAC) pain subscale at 12 weeks. Secondary outcomes include weekly WOMAC pain, function and stiffness scores, patient and physician global assessments, lower-extremity function, knee proprioception, depression, self-efficacy, social support, health-related quality of life, adherence and occurrence of adverse events after 12, 24 and 48 weeks.

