## Methods/Design

### Study design

This study is a single-blinded, randomized, attention-controlled, clinical trial to evaluate the physical and psychological effects of Tai Chi for patients suffering from tibiofemoral KOA. Our goal is to compare the safety and effectiveness of Tai Chi with an attention control (wellness education and stretching program) in 40 patients with KOA. (The "single-blind" study design has been decided upon because of the inability to conceal Tai Chi assignment allocation from participants and the instructors in Tai Chi clinical trials. However, all study evaluators will be masked to treatment assignment throughout the duration of the study.)

Outcome parameters compare changes in knee pain, stiffness, and physical function using the well-validated Western Ontario and McMaster University Index (WOMAC), patient and physician global assessments, lower-extremity function, knee proprioception, depression, self-efficacy, social support, health-related quality of life, outcome expectation, adherence and occurrence of adverse events. Outcome measurements are performed at baseline, every week during the intervention period, and on completion of the 12-week program, in addition to the 24 week and 48 week follow-up. Study evaluators (study rheumatologist, study coordinator, exercise physiologist and statistician) are masked to treatment assignment.

The study setting is located in an urban tertiary care academic hospital (Tufts Medical Center) in Boston Massachusetts. The study has received Ethics approval from the Tufts Medical Center/Tufts University Human Investigation Review committee and will be conducted in the Clinical Research Center and Division of Rheumatology at Tufts Medical Center.

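### Last observation carried forward is justified as biasing towards the null, but at weeks 24 and 48 it favours Tai Chi if the between-group difference wanes

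*Protocol article*

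**What the plan says.** The Statistical Analysis section sets the endpoints: "The primary outcome is the measurement of change in knee pain between baseline and 12 weeks", and "Secondary outcomes are measurements of change at 24 weeks and 48 weeks". It adds: "These will be analyzed both as individual time points and in longitudinal analyses". The analysis sets are fixed as follows: "Analyses will be intention-to-treat with secondary analyses based on completers".

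For patients who withdraw, there are two steps. First, "every effort will be made to complete a follow-up WOMAC and clinical knee examination at the time of withdrawal". If that assessment cannot be obtained, "we will carry forward the last assessment of knee pain, physical function or as a conservative assessment to bias towards the null hypothesis". Nothing restricts this rule to the week-12 endpoint, and no argument is given for the direction of bias that it claims.

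Three other places decide which value would be carried:

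- Study design: "Outcome measurements are performed at baseline, every week during the intervention period, and on completion of the 12-week program". Table 1 marks WOMAC pain during the intervention.
- Intervention: classes in both arms run for 12 weeks. Weeks 24 and 48 are follow-up visits.
- Discussion: 20 patients per arm are described as having completed the study through week 48, with the analysis still to be done.

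**The concern.** The direction of bias from carrying a score forward depends on two things: what would have happened to the patient after that score, and how many patients leave each arm. The rule biases towards no effect only if the carried between-group difference is smaller than the true one at the endpoint. That is plausible during a 12-week course in which benefit builds up. It is not a safe assumption for weeks 24 and 48. A patient lost after the classes end carries a score from around the time of greatest class exposure, and any later fading of benefit is erased from the analysis.

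Durability is at stake. The Background criticises earlier trials for short follow-up and offers one-year follow-up as the improvement. If losses occur and benefit fades, the analysis would show part of a lasting effect that is not there, and the report would describe that result as conservative.

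A second issue is precision. Carried values enter the analysis as if they had been measured at the endpoint.

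**Working it through.** **Inputs.** From the Sample size section: mean changes -79 (SD 91) and -20 (SD 77), 20 per group, alpha 0.05, difference -59, power 60%. The article gives no dropout rate for this trial, so loss rates are assumed (5% to 35% per arm). The amount of waning and the correlation between visits (0.6) are also assumed.

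**1. The plan's own figure.** Pooled SD = sqrt((91² + 77²)/2) = 84.29. SE = 84.29 × sqrt(2/20) = 26.66. 59/26.66 - 1.96 = 0.25, which gives two-sided power of 60.0%. The stated 60% reproduces, so these means and SDs are a sound base.

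**2. Week 12.** Let dT and dC be the dropout in the Tai Chi and control arms, and let dropouts carry a fraction f of their arm's gain. Then

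estimate = -59 + (1 - f) × (79·dT - 20·dC).

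| Dropout, Tai Chi / control | Baseline carried (f = 0) | Half the gain carried (f = 0.5) |
|---|---|---|
| 10% / 10% | -53.1 | -56.1 |
| 20% / 20% | -47.2 | -53.1 |
| 30% / 30% | -41.3 | -50.1 |
| 10% / 30% | -57.1 | -58.1 |
| 5% / 25% | -60.0 | -59.5 |

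With equal dropout the effect shrinks, as the plan says. It is exaggerated once 20·dC exceeds 79·dT, that is, once dC/dT exceeds 79/20 = 3.95. If the two arms truly improve equally, any excess of control dropout favours Tai Chi. With both arms improving by 79, dropout of 5% against 35% and half the gain carried, the false difference is 0.5 × 79 × (0.05 - 0.35) = -11.9.

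**3. Week 48.** Let a proportion p of each arm be lost after the week-12 score, with that score carried. Then

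estimate = (1 - p) × (true 48-week difference) + p × (-59).

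| Loss per arm | True difference 0 | True difference -29.5 |
|---|---|---|
| 10% | -5.9 | -32.5 |
| 20% | -11.8 | -35.4 |
| 30% | -17.7 | -38.3 |

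If the full -59 persists, the estimate is -59 and there is no bias. The bias is p times the fall in the between-group difference since the carried visit. It needs no imbalance in dropout. The same formula applies at week 24.

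**4. Effect on the test.** Simulation with 8,000 replicates, 20 per arm, SDs 91 and 77, dropout unrelated to outcome, and a true 48-week difference of 0: two-sided rejection at the 5% level was 7.6% with 20% loss and 9.9% with 30% loss. Of these, 6.5 and 9.4 percentage points favoured Tai Chi. Completers stayed at 5.0%. A regression estimator valid when data are missing at random (MAR) averaged -0.1 and 0.2.

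**5. Precision.**

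| Setting | SE reported with carried values | SD of the MAR estimator |
|---|---|---|
| Week 12, 20% loss | 25.9 | 28.6 |
| Week 12, 30% loss | 25.5 | 30.6 |
| Week 48, 20% loss | 27.2 | 28.9 |
| Week 48, 30% loss | 27.3 | 30.9 |

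The carried-forward SE is about 6% to 17% lower. At week 12 it falls below the value with no missing data (about 26.5). Part of that comes from the simulation's assumption that mid-course change has 0.8 times the endpoint SD.

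**The case against.** The strongest reply is that the plan is right about its primary endpoint. On its own means, equal dropout at week 12 shrinks the effect, and reversal needs roughly four times as many control dropouts. That stands: a reader might infer that the rule inflates the week-12 result, and the design figures do not support this without a marked imbalance or arms that improve alike.

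Four further points also stand:

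- Carrying forward is a fallback after an attempted withdrawal assessment, and completer and longitudinal analyses are also planned. The losses above count only patients whose values are actually carried. But the completer analysis is secondary, and a withdrawal visit may be unobtainable for a patient lost after week 12.
- A reader might picture patients who improve early, relapse and leave, and are then analysed as improved. With weekly pain scores the relapse would normally show in the last score. The story needs a relapse that those scores miss and a failed withdrawal assessment.
- A reader might infer from Table 1, which marks no physical function during the intervention, that week-12 function would always carry baseline. The Abstract says otherwise: "Secondary outcomes include weekly WOMAC pain, function and stiffness scores". The two places disagree, so the inference is not secure.
- A reader might infer that the standard error is wrong for the estimator used. It is not: at week 12 with 20% loss, the reported 25.9 agrees with a sampling SD of 25.6. The shortfall is in the uncertainty about the true endpoint difference.

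Finally, if the Discussion means that all 40 patients gave week-48 data, the rule is never used. The text speaks of completing the study and does not state that outcome data are complete, so this limits the likely impact without settling it. The trial is also declared preliminary and underpowered.

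**Conclusion.** The concern holds as a wrong justification for a fixed rule. Carrying the last score forward is not guaranteed to bias towards the null in this design. It does so at week 12 under similar dropout and growing benefit. At weeks 24 and 48 it favours Tai Chi whenever the between-group difference wanes after patients are lost. The size is -5.9 to -17.7 points for 10% to 30% loss if the difference disappears entirely, and -35.4 instead of -29.5 for 20% loss if it halves. Uncertainty about the true difference is understated as well.

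These sizes rest on assumed loss rates and assumed waning; the article supports neither with a figure. They also assume that the losses fall after the week-12 score and before the next visit. The documents do not show that any reported result is biased, and the practical effect may be nil. The correction is worth making because it is cheap and the stated rationale is wrong, but the validity of the primary comparison does not depend on it.

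**What to change.** 1. Delete the statement that carrying forward is conservative or biases towards the null.
2. Make the main intention-to-treat analysis a likelihood-based longitudinal model of all observed WOMAC pain scores, with baseline as covariate, visit as a categorical factor and a treatment-by-visit interaction. The week-12 contrast is primary. Visit should be categorical because a straight line in time would misfit a benefit that rises and then fades. Multiple imputation from baseline and weekly scores is an acceptable alternative.
3. Enter withdrawal assessments at their actual date; do not move them to the endpoint.
4. Keep carrying forward only as a sensitivity analysis, beside one in which dropouts return to baseline. Label neither as conservative. Returning dropouts to baseline also favours Tai Chi if both arms improve by 79 and dropout is 10% against 30%: 79 × (0.10 - 0.30) = -15.8.

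The cost is some analysis wording, a little programming and possibly slightly wider intervals. With 40 patients and weekly visits the covariance between visits will need a simple structure. No new data are required, and if no values are missing the missing-data rule changes nothing.

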## Discussion

In this article, we present the challenges of designing a randomized controlled trial with long-term follow up. The challenges encountered in this design are: strategies for recruitment, avoidance of selection bias, the actual practice of Tai Chi, and the maximization of adherence/follow-up while conducting the clinical trial for the evaluation of the effectiveness of Tai Chi on KOA.

A total of 40 eligible patients, 20 with Tai Chi and 20 with an attention control (wellness education and stretching) have already completed the study including 3 month recruitment, 12 week intervention, as well as 24 and 48 week follow-up at the Tufts Medical Center. We will perform analysis of the data and report the findings. Therefore, this project will provide important preliminary data on physical and psychological effects of Tai Chi for KOA. It will establish rigorous methods for future research for testing the mechanisms by which Tai Chi may influence pain, disability, and health related quality of life in people with KOA.
